### Data management, storage, monitoring, and dissemination

Data is collected with a unique identifier for each patient (i.e., pseudonym) using the online survey software program Qualtrics [115] and the web tool Lotus, which has been especially developed for longitudinal research by the University of Amsterdam. The list of pseudonyms and personal information of patients within a particular mental healthcare center is securely stored at the center and only accessible for the research assistant and coordinator of this center. A different set of pseudonyms is used for data collected by clinicians (i.e., intake questionnaire and recordings). The list with the combination of both pseudonyms of patients is only accessible for the research assistant and coordinator of the center and the authorized researchers. The data is stored on a secure storage server of the University of Amsterdam, accessible only to authorized researchers.

All (serious) adverse events reported by the patient or observed by clinicians or researchers will be recorded. There is no data monitoring committee and the study will not be audited. The results of the study will be disseminated in scientific journals and presentations at (inter)national scientific conferences.

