All assessments are performed by trained local research assistants blind to the patients’ treatment condition, with exception of the SCID-5 interviews, demographic interview, and cost interview. The SCID-5 interviews can be administered by trained research assistants as well as trained intake staff members, both blind for condition. The demographic interview and cost interview contain questions on healthcare utilization and are therefore performed by non-blinded local research assistants. Due to the nature of the interventions, blinding of therapists and patients is not possible. All interviews, except for the SCID interviews, are audio-recorded. Participants receive financial compensation for their involvement in the study. Patients who discontinue their treatment or deviate from the treatment protocol will be encouraged to continue the assessments.

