### Treatments

#### Format

For patients of both DBT and ST, treatment has a maximum duration of 25 months and starts with a pretreatment phase of approximately four weeks consisting of several (ST: ± three; DBT: ± five) individual sessions in which patients are prepared for the group sessions and become accustomed to their therapists and the treatment model. After the pretreatment phase, patients receive a combined program of individual sessions and group sessions (i.e., treatment phase). Group sessions of both treatments are offered in a semi-open format. If treatment slots are available, new patients can enter the ST group every 10 weeks and for DBT groups at the start of a mindfulness skills module. In DBT, the treatment phase has a maximum duration of 12 months and consists of weekly group sessions (i.e., skills training groups; 150 min), weekly individual psychotherapy sessions (50 min), and between-session consultation. The between-session consultation, often called telephone consultation although all kinds of technology can be used [95], is offered to the patient within limitations set by the individual therapist, varying between access to between-session support within working hours to 24/7 access to between-session support, which is officially the standard in DBT. In ST, the treatment phase has a maximum duration of 18 months consisting of weekly group (90 min) and individual (45 min) psychotherapy sessions for a period of 12 months, continued by weekly group psychotherapy sessions and biweekly individual psychotherapy sessions for a period of six months. Following the treatment phase, patients continue their treatment with a maintenance phase. The maintenance phase of DBT is a recently developed blended aftercare program with a maximum duration of 12 months. The blended aftercare program was developed based on results of previous studies (e.g., [31, 96]) and recommendations by several authors (e.g., [96–98]) to extend the duration of DBT to sustain or even enhance treatment effects. The DBT aftercare program consists of monthly individual psychotherapy sessions, three-monthly group sessions, and an eHealth intervention in which patients have online access to DBT handouts and worksheets [99]. The maintenance phase of ST consists of biweekly individual psychotherapy sessions for a period of three months, continued by three months of one individual session each month. Disregarding the time spent on telephone consultation, homework assignments, and eHealth, and based on 48 working weeks a year, patients will receive about 167 h of treatment if they follow the treatment protocol. Patients who have completed treatment successfully before they reach the maximum number of treatment sessions are allowed to complete treatment earlier, although the assessments will be conducted at the originally planned assessment points. Early termination of treatment requires substantial improvements in the primary and secondary outcomes and is decided in joint decision by the patient and therapist. The treatments are covered by the public health insurance. See Table 2 for an overview of the treatment formats.

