##### Costs

Costs, including healthcare costs, patient and family costs, and costs outside the healthcare sector, are measured using a retrospective cost interview especially designed for BPD patients [80]. Healthcare costs include visits to general practitioners, hospitals, crisis centers, psychologists and psychiatrists, use of medication, social work, paramedical care, and alternative treatments. Patient and family costs include informal care (i.e., care provided by the patient’s family, friends, or neighbors) and out of pocket costs (e.g., drugs, alcohol, excessive spending). Costs in other sectors include productivity losses from unpaid work (study and voluntary work) and paid work. Since it is difficult to distinguish between BPD-related costs and costs due to other psychological disorders [17], only a distinction will be made between costs due to psychological disorders and costs due to somatic diseases. The cost interview will be conducted by trained research assistants using a recall period of six months (baseline assessment), the number of weeks since randomization (assessment six months after start of the treatment phase), or the number of weeks since the previous assessment (assessments 12, 18, and 24 months after start of the treatment phase and both follow-up assessments).

Dutch guidelines [186, 187] will be used to determine total costs. Healthcare costs will be calculated by volumes of resource use multiplied by their corresponding unit costs, derived from Hakkaart-van Roijen et al. [186]. Prescribed medication costs will be determined based on national reference prices. Informal care costs will be computed by multiplying the number of hours the patient receives informal care by shadow prices [186]. Shadow prices will also be used to value lost productivity in study and voluntary work. Productivity losses from paid work will be valued according to the Human Capital Approach [188]. Out of pocket costs, such as alcohol and excessive spending, will be directly retrieved from the cost interview or, in case of over-the-counter medication, from the Dutch Pharmacotherapeutic Compass [186].

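### The article states no fixed adverse-event inquiry at the common assessments, and scheduled therapist contact differs by arm (36 v 8 sessions in months 12–18), so between-arm event counts may be affected by unequal detection

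*Protocol article*

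**What the plan says.** The rule for safety data is in the Protocol article, Data management, storage, monitoring, and dissemination: "All (serious) adverse events reported by the patient or observed by clinicians or researchers will be recorded". The sentence names three sources (patient, clinician, researcher). It gives no set questions, checklist or interval. The same section states that there is no data monitoring committee and no audit, and Statistical analyses plans no interim analysis.

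The therapy schedules are under Treatments, Format, and in Table 2.

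- **First 12 months, ST:** "weekly group (90 min) and individual (45 min) psychotherapy sessions for a period of 12 months".
- **First 12 months, DBT:** "In DBT, the treatment phase has a maximum duration of 12 months and consists of weekly group sessions (i.e., skills training groups; 150 min", together with "weekly individual psychotherapy sessions (50 min), and between-session consultation".
- **Months 12–18, ST:** "continued by weekly group psychotherapy sessions and biweekly individual psychotherapy sessions for a period of six months".
- **From month 12, DBT:** "The DBT aftercare program consists of monthly individual psychotherapy sessions, three-monthly group sessions, and an eHealth intervention".
- **Months 18–24, ST:** biweekly individual sessions for three months, then monthly ones for three months.

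Research contact is the same in both arms: interviews with questionnaires every six months during treatment, some self-report every three months, and two follow-ups (Procedure and assessments). That section also says: "The demographic interview and cost interview contain questions on healthcare utilization and are therefore performed by non-blinded local research assistants". Under Costs, the recall window runs from randomization for the six-month assessment. For each later one it is "or the number of weeks since the previous assessment".

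**The concern.** A clinician can observe an event only where there is contact, and many patient reports are also likely to be made to a therapist. If contact differs by arm and no common inquiry backs it up, equal true event rates can yield unequal recorded counts.

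This population makes the matter practical. The Background cites suicide attempts or threats in up to 84% of patients and suicide in 3–6%, or even up to 10%. The Discussion cites a hypothesis that DBT may reduce self-harming and suicidal behavior better and faster than ST. Readers will want to compare such events by arm, and the article describes nothing that would reveal unequal capture. The primary BPDSI-5 analysis is not at issue here.

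**Working it through.** **Inputs.** Session frequencies, session lengths and the 48-week working year come from Format and Table 2. That year gives 24 weeks per half-year and 12 per quarter. Pretreatment is taken as 3 ST and 5 DBT sessions. Lengths are 90 min (group) and 45 min (individual) in ST, and 150 and 50 min in DBT. The article gives no session lengths for pretreatment or maintenance, so the same lengths are assumed there.

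**The article's own contact figure.** Format gives about 167 h per patient.

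- ST: 2.25 + 108 + 45 + 6.75 = 162.0 h (3.0% below 167).
- DBT: 4.17 + 160 + 20 = 184.2 h (10.3% above 167).

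The stated figure is thus roughly met for ST but not for DBT. That is a separate matter, because the session counts below do not use it.

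**Sessions by period.**

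- Months 0–12: ST 48 group + 48 individual = 96; DBT 48 + 48 = 96.
- Months 12–18: ST 24 group + 24/2 individual = 36; DBT 6 individual + 2 group = 8. Ratio 36/8 = 4.5.
- Months 18–24: ST 12/2 + 3 = 9; DBT 6 + 2 = 8.

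| Period | Sessions ST v DBT | Ratio | Hours ST v DBT | Ratio |
|---|---|---|---|---|
| Pretreatment | 3 v 5 | 0.60 | 2.25 v 4.17 | 0.54 |
| Months 0–12 | 96 v 96 | 1.00 | 108 v 160 | 0.68 |
| Months 12–18 | 36 v 8 | 4.50 | 45 v 10 | 4.50 |
| Months 18–24 | 9 v 8 | 1.12 | 6.75 v 10 | 0.68 |
| Whole programme | 144 v 117 | 1.23 | 162 v 184.2 | 0.88 |

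Between-session consultation in DBT is not counted. It ranges from working hours only to 24/7, depending on center and therapist. Its targets include self-harm and suicidal behavior (Discussion), so it adds visibility in the DBT arm in year 1. Adding the month-15 and month-18 research contacts to months 12–18 gives 38 v 10, or 3.8-fold.

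**What the common assessments cover.** The BPDSI-5 looks back three months and is given every six. The month-12 interview reaches back to month 9 and the month-18 interview to month 15, so months 12–15 are not covered. The cost interview covers hospital and crisis-center use over the whole interval. Nothing in the article says that answers from either interview enter the adverse-event record.

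**Why no effect size follows.** The document gives no event rate and no detection probability. Suppose, purely as an assumption, that an event surfaces with probability p at each session, so that capture = 1 − (1 − p)^sessions.

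- If it can surface only within one month (24 + 12 = 36 sessions over 6 months gives 6 a month in ST; 8/6 = 1.33 in DBT), capture is 46.9% v 13.1% at p = 0.1, 88.2% v 37.8% at p = 0.3 and 98.4% v 60.3% at p = 0.5. The ratios are 3.6, 2.3 and 1.6.
- If an event at month 12 can surface at any session in the next six months (36 v 8), the ratios fall to 1.7 (97.7% v 57.0%), 1.06 and 1.00.

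The answer runs from 1.00 to 3.6 according to assumptions that the document cannot settle. None of these figures is an estimate for this trial.

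**The case against.** The strongest objection is that this is one sentence in a condensed article. Protocol version 07 is active and not shown, and how events are elicited is commonly left to it. That stands as a limit on the point. It does not remove it, because the article states a capture rule, and nothing shown links the shared assessments to the event record.

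Several stronger readings are tempting, and the document does not support them:

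- **Events are caught only if volunteered or noticed by chance.** The text does not say so. A patient can report when asked, and researchers are a named source who see both arms on one schedule. Patients who finish early keep the planned assessments, and those who discontinue are encouraged to continue them.
- **The cost interview is not used for adverse events.** The article is silent on this. An admission mentioned there to a research assistant would fall under the stated rule.
- **The event record is the only safety evidence.** Hospital and crisis-center use is collected identically in both arms. The BPDSI-5 rates all nine BPD criteria; that this reaches self-harm and suicidal acts is an inference from those criteria.
- **Dropout and follow-up add an arm difference.** The dropout rate of up to 30% comes from earlier studies and is not shown to differ by arm. In follow-up, scheduled therapy ends in both arms.
- **Blinded assessors will be unblinded by event reports.** The article does not assign event reports to BPDSI-5 assessors. Naming the recipient is a precaution only.

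It is also fair to say that 4.5 describes the worst six months, and that the article lists no between-arm analysis of event counts. What remains is the contact asymmetry and the absence of a stated common inquiry.

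**Conclusion.** The point holds in limited form. The article states no fixed adverse-event inquiry at the common assessments, and scheduled therapist contact differs by arm by design. The gap peaks at 36 v 8 sessions in months 12–18. Any between-arm comparison of event counts may therefore be affected by unequal detection, most plausibly in that window.

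A reader might infer that event counts will track contact rather than harm, or will favor one arm throughout. Neither is shown. Over the programme ST has 1.23 times the sessions but 0.88 times the hours, and DBT has added consultation in year 1, so no overall direction is fixed. Opposite asymmetries in different periods cannot be relied on to cancel either.

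The session counts rest on the 48-week year and full attendance; on a 52-week year the peak ratio is 39/8 = 4.88. The size of any distortion cannot be computed from the document. The change is worth making because it is cheap, but the point does not threaten the main analyses.

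**What to change.** In Data management, storage, monitoring, and dissemination, add a short, identical set of (serious) adverse-event questions, covering for example suicide attempts, self-harm needing care, admissions and crisis contacts.

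- **Who and when:** the non-blinded assistant asks them at every cost interview after randomization, in both arms, over the window already in use (since randomization, then since the previous assessment). Patients who stopped treatment are included.
- **Use:** this scheduled source is the primary basis for any between-arm safety comparison. All other reported or observed events, including deaths notified by a relative or center, are still recorded and are listed separately.
- **Routing:** event reports go to non-blinded staff rather than to the BPDSI-5 assessors.

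The cost is a few minutes per interview and a small amendment, using staff and visits already in place. The drawback is a mixed record: events collected before the change must be flagged as such, or be recalled over a longer window. If protocol version 07 already contains such an inquiry, one sentence in the article saying so is enough.

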### Measures

The instruments include screening measures, measures to assess potential predictors and mediators of treatment response, and outcome measures. The instruments that were not available in Dutch were translated (i.e., Brief Experiential Avoidance Questionnaire, Dialectical Behavior Therapy-Ways of Coping Checklist, Gordon Test of Visual Imagery Control, Positive Mental Health scale, and social problems) by bi-lingual experts. The translations were checked for consistency with the original version. Items, questionnaires, and interviews that have been developed or modified by the authors are available upon request by the first author.

#### Screening

##### Mental disorders

The SCID-5 is a semi-structured interview used to diagnose DSM-5 disorders. Personality disorders are assessed with the SCID-5-PD [116] and syndrome disorders are assessed using the SCID-5-S [117], which is an extended version of the SCID-5 Clinician Version (SCID-5-CV; [118]). Additional file 3 offers an overview of all syndrome disorders that are assessed by the SCID-5-S. Based on a first psychometric evaluation in a psychiatric patient sample, Somma et al. [119] found an adequate interrater reliability of the SCID-5-PD. In addition, the SCID-5-CV has demonstrated good psychometric properties [120–122].

Before administering the SCID-5-S and/or SCID-5-PD, self-report screening questionnaires (SCID-5-SPQ; [123], and SCID-5-SV; [124]) may be administered. In accordance with the instructions for administering the SCID, disorders and criteria of disorders not affirmed by the screening questionnaires and not considered as false negatives by the clinician will be assumed to be absent. The SCID-5 will be assessed during the screening phase and 12 months after end of the treatment.

##### Motivation and availability

A 13-item semi-structured motivation interview is used to assess several exclusion criteria (e.g., no fixed address, have received ST or DBT in the past year) and patient’s motivation and availability.

#### Predictors

As mentioned, candidate predictor variables of (differential) treatment response have been selected using a multi-method approach (i.e., literature, suggestions of a patient representative of the Borderline Foundation of the Netherlands, and semi-structured interviews with 18 expert clinicians). Additional file 4, Table 1 offers an overview of the predictors that have emerged during the semi-structured interviews with clinicians. Additional file 4, Table 2 offers an overview of the predictors based on the literature and suggestions of a patient representative. The candidate predictors of (differential) treatment response are assessed at baseline. Only the measures that are not part of the screening, mediator or outcome measures will be briefly described in this paragraph.

##### Autistic traits

Autistic traits are assessed by the abbreviated version of the Autism Spectrum Quotient, the AQ-10 [125]. The AQ-10 consists of 10 items rated on a four point Likert scale. The AQ-10 has demonstrated acceptable psychometric properties in an adult general population sample [126].

##### Commitment

Patient commitment to treatment is measured with a selection of items of the subscale Motivation to Engage of the Treatment Motivation Scales for forensic outpatient treatment (TMS-F; [127]). The four items can be rated on a seven point Likert scale.

##### Experiential avoidance

The Brief Experiential Avoidance Questionnaire (BEAQ; [128]) is a 15-item scale assessing experiential avoidance across six domains (i.e., behavioral avoidance, distress aversion, suppression, procrastination, repression/denial, and distress endurance). The items can be rated on a six point Likert scale. The BEAQ has shown good psychometric properties among psychiatric outpatients [128].

##### Frustration intolerance

Frustration intolerance is assessed by the Frustration Tolerance subscale of the Severity Indices of Personality Problems (SIPP-118; [129]). This subscale consists of eight 4-point Likert scale items measuring the capacity to cope with setbacks and disappointments. In previous research among Dutch patients with a personality disorder, the subscale demonstrated moderate to good reliability [129].

##### Insight

A modified version of the Self-Reflection and Insight Scale (SRIS; [130, 131]) is used to assess self-reflection and insight. The SRIS contains 20 five point Likert scale items. The SRIS has shown good reliability and validity in student samples [130, 132].

##### Internal locus of control

Internal locus of control, defined as the extent to which a person experiences an outcome as the result of their own behavior or personal characteristics rather than external circumstance, is assessed by the Locus of Control scale (IE; [133]). The IE contains 10 five point Likert scale items. Previous research has demonstrated adequate psychometric properties [133, 134].

##### Level of personality functioning

The Level of Personality Functioning Scale-Brief Form 2.0 (LPFS-BF 2.0; [135]) assesses impairment in personality functioning according to the DSM-5 alternative model for personality disorders. The LPFS-BF 2.0 contains 12 four point Likert scale items. Based on a first psychometric evaluation among Dutch patients referred to a specialized mental healthcare center for personality disorders, the LPFS-BF 2.0 has demonstrated satisfactory psychometric properties [135].

##### Mental imagery capacity

Mental imagery capacity is assessed with the 12-item Gordon Test of Visual Imagery Control (TVIC; [136]). The TVIC assesses the ability to visualize and manipulate a given scenario in response to a set of cues. Participants can response on a three point Likert scale. In addition to the 12 Likert scale items, we measure the time it takes the participant to visualize the scenarios. Finally, we have added two 100 mm visual analog scale (VAS) items measuring how well participants see the scenarios that were described and how difficult it was for the participant to visualize the different scenarios. The TVIC has demonstrated fair to satisfactory internal consistency and validity among community samples and undergraduates [137–140].

##### Mentalizing capacity

Mentalizing capacity is measured using an eight-item version of the Reflective Functioning Questionnaire (RFQ-8; [141]). The RFQ-8 comprises two dimensions: uncertainty about mental states, reflecting hypomentalizing, and certainty about mental states, indicating hypermentalizing. The RFQ-8 uses a seven point Likert scale. In previous research among BPD patients, the questionnaire has demonstrated satisfactory psychometric properties [141–143].

##### Perfectionism

The eight-item Frost Multidimensional Perfectionism Scale-Brief (F-MPS-Brief; [144]) assesses perfectionism across two dimensions (evaluative concerns and striving). Items are rated on a five point Likert scale. Psychometric properties of the F-MPS-Brief were found to be good in clinical and community samples [144].

